#### Sample Size Calculation

To determine the sample size needed, we based our effect size estimates on previous studies [17,56] that have similarly evaluated the impact of interrupting prolonged sitting on glucose iAUC. These studies reported a 20%-30% decrease in iAUC level for the intervention groups. Therefore, for the WorkWell Study, we used a conservative estimate of 15% difference between baseline and the 2 intervention measurements (with a 1% population estimate of SD). Using G*Power software (version 3.1.9.2) [57], we estimated that we will have to recruit 15 individuals (allowing for 80% retention) to obtain a final sample size of 12 participants (α=.05, power=80%).

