## Methods

### Study Aims

The primary aim of this study is to examine the impact of 2 different intervention conditions (STAND and MOVE) on 3-hour postlunch postprandial glucose compared to the baseline control condition. Interventions entail adding 6 minutes per hour to baseline standing and LPA minutes during the workday. We hypothesize that both intervention conditions will improve postprandial glucose regulation. The secondary aim is to assess intervention adherence and changes in standing and LPA. Exploratory aims include (1) assessing participant acceptability and satisfaction during the intervention; and assessing intervention-induced changes in (2) sleep, (3) anthropometrics and body composition, (4) endothelial function, (5) central and peripheral blood pressure, (6) fasting blood glucose concentration, (7) fasting insulin concentration, (8) fasting high-density lipoprotein (HDL) concentration, (9) low-density lipoprotein (LDL) oxidation, (10) fasting triglycerides, (11) total antioxidant capacity (TAC), (12) hemoglobin A_1c_ (HbA_1c_), (13) microbial diversity of the gut, (14) metabolomics from stool and plasma, and (15) DNA variants that may explain differences in response to the intervention.

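### The printed SD of 1%, N of 12 and power of 80% cannot all hold, so the power claim for the primary outcome cannot be traced to its inputs

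*Protocol article*

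**What the plan says.** The Sample Size Calculation section starts from earlier studies of interrupted sitting: "These studies reported a 20%-30% decrease in iAUC level for the intervention groups". It then takes a smaller effect for this trial: "we used a conservative estimate of 15% difference between baseline and the 2 intervention measurements (with a 1% population estimate of SD"). The tool is named ("Using G*Power software (version 3.1.9.2"), and the result is that "we will have to recruit 15 individuals (allowing for 80% retention") "to obtain a final sample size of 12 participants (α=.05, power=80"%).

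The section does not state the test family, the sidedness, the within-person correlation, a standardized effect, or whether the SD is that of a single measurement or of a within-person difference. The Statistical Analysis Plan section adds that there are three repeated measurements per person and that the primary outcome is postprandial glucose iAUC. The Study Aims section states the hypothesis: "We hypothesize that both intervention conditions will improve postprandial glucose regulation".

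**The concern.** The effect and the SD stand in one sentence and both are percentages, so a reader will divide one by the other. The ratio is 15, a size of effect for which a sample size calculation is hardly needed. A sample of 12 and a power of 80% belong to a much smaller standardized effect.

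This section is the only justification in the article for recruiting 15 people and for the power of the primary comparison. If its inputs do not lead to its result, readers cannot tell what difference in iAUC the trial can detect. A null result would then be hard to interpret: a 15% difference might have been reasonably excluded, or might never have been detectable.

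**Working it through.** **Inputs from the article.** Difference 15%; SD 1%; α = .05; completers 12; power 80%; retention 80%; recruited 15 (all Sample Size Calculation); 3 measurements per person (Statistical Analysis Plan). Sidedness, test family, correlation ρ and type of SD are not stated, so each was varied.

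**1. Retention step.** 12 / 0.80 = 15. This reproduces.

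**2. Paired test on the stated inputs.** Standardized effect dz = difference / SD of the difference. Power comes from the noncentral t distribution with n − 1 degrees of freedom and noncentrality dz·√n.

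- If 1% is the SD of the difference, dz = 15 / 1 = 15. Two-sided power is 90.4% at n = 2, above 99.99% at n = 3, and essentially 100% at n = 12.
- If 1% is the SD of a single measurement, the SD of the difference is 1% × √(2(1 − ρ)). Then dz = 15 / √2 = 10.6 at ρ = 0, 15 at ρ = 0.5, and 33.5 at ρ = 0.9. At dz = 10.6, power is 76% at n = 2 and above 99.99% at n = 3.

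**3. Repeated-measures F test on the stated inputs.** Take means of 0, −15 and −15. Their SD (divisor 3) is 7.07, so f = 7.07 / 1 = 7.07. With noncentrality λ = f²·n·3 / (1 − ρ) and degrees of freedom 2 and 2(n − 1), power already exceeds 99.9% at n = 2, even at ρ = 0.

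The stated inputs therefore call for 2 or 3 participants in these variants. They do not give 12, and power at 12 is not 80%.

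**4. What would give 12 at 80%?**

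- Paired, two-sided: dz = 0.889, so the SD of the difference is 15 / 0.889 = 16.9%.
- Paired, one-sided: dz = 0.766, so 15 / 0.766 = 19.6%.
- F test over 3 measurements: f = 0.555 at ρ = 0, 0.392 at ρ = 0.5, and 0.175 at ρ = 0.9. With 7.07 / f, the SD of a single measurement is about 12.7%, 18.0% and 40%.

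These SDs are back-solved, not figures from the article. All are more than ten times the printed 1%.

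**5. Could other inputs lie behind the 12?**

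| Reading | N for 80% power |
|---|---|
| SD = 1 in place of 1%, so d = 0.15, paired | 351 two-sided, 277 one-sided |
| f = 0.15, 3 measurements | 73 at ρ = 0.5; 16 at ρ = 0.9; 12 at ρ = 0.93 |
| f = 0.25, 3 measurements | 12 at ρ = 0.8 |
| f = 0.4, 3 measurements | 12 at ρ = 0.5 |

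Some entries do give exactly 12, but the article states none of these f values or correlations.

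**6. How much depends on the missing SD.** Power at n = 12 for a 15% difference (paired, two-sided .05), with the SD of the difference assumed:

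| Assumed SD of difference | Power at n = 12 |
|---|---|
| 10% | 99.7% |
| 15% | 88% |
| 20% | 66% |
| 25% | 47% |
| 30% | 35% |
| 40% | 22% |

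The table is illustrative. Nothing in the article favours one row over another.

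**The case against.** The best defence is that the calculation was sound and only its description is wrong. The article names neither the test family nor the correlation, and step 5 shows plausible G*Power entries that return exactly 12. This stands. It means that the calculation itself cannot be called wrong, and that it would be false to say no reading of the inputs recovers 12. It does not rescue the printed sentence, because the SD it gives is not an input that leads to 12.

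A reader might go further and infer that the trial is underpowered. The article does not support that. Taken literally, its inputs imply near-certain detection, and the low powers in step 6 come from assumed SDs. At an assumed SD of 10%, 12 completers would be ample.

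A reader might also take the 80% as a per-comparison figure and conclude that the chance of both interventions reaching significance is lower. The article describes a difference between baseline and the two intervention measurements. That fits an omnibus test over three measurements, or baseline against the pooled interventions, as well as it fits separate comparisons. The Study Aims section hypothesizes that both conditions help, but no section makes joint significance the criterion for success, and any joint figure would need an assumed correlation.

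It can also be said that this is a pilot, that the Results section reports enrolment completed in March 2023, and that a condensed article leaves detail to a fuller plan. The first two limit the consequences: no design decision is still open. The third does not apply, because the problem is a printed input that conflicts with the printed result, and a fuller document cannot make those figures agree.

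**Conclusion.** The point holds as an inconsistency in the stated justification. A 15% difference, a 1% SD, 12 completers and 80% power cannot all be true together. On the stated inputs, 2 or 3 participants suffice and power at 12 is essentially 100%. For a two-sided paired comparison at .05, a sample of 12 at 80% power needs an SD of the difference of 16.9%, about 17 times the printed value. The conclusion that the inputs do not reproduce the result rests on the printed figures alone; it holds whether the 1% is the SD of a difference or of a single measurement, for correlations from 0 to 0.9.

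Whether 12 completers are enough to detect 15% cannot be settled from the article. It depends on an SD of the within-person difference that the article does not usably give. The correction should be made because this is the only support for the power of the primary outcome.

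**What to change.** Replace the 1% SD with what was actually entered in G*Power: either the SD of the within-person difference, or f together with the within-person correlation. Name the test family and the sidedness, and say whether the 80% refers to an omnibus, a pooled or a per-comparison test.

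If those inputs cannot be recovered, withdraw the claim of 80% power for a 15% difference. State in its place that, for a two-sided paired comparison at .05, 12 completers give 80% power for a standardized effect of about 0.89, which corresponds to 15% only if the SD of the difference is about 17% or less. Print power over a range of assumed SDs on both sides of that value, such as 10% to 40%, labelled as illustrative.

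The cost is a change of text and numbers. Enrolment and the analysis model stay as they are. The stated power may become less favourable.

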### Ethics Approval

This study has been reviewed and approved by the institutional review board at Arizona State University (STUDY00010172) as well as registered on ClinicalTrials.gov (NCT04269070). Screening consent will be obtained prior to in-person screening visit and subsequent full-informed consent will be obtained from all qualifying participants prior to enrollment. All participant information and data will be deidentified and assigned an identification number in which all subsequent data, samples, and surveys will be labeled to ensure confidentiality. As a part of the study intervention, participants will be provided lunchtime meals during the work week as well as up to US $65 in a web-based gift card of their choice for completion of the study.

## Results

Recruitment is ongoing as of January 2023. To date, 10 participants have been enrolled, with 2 withdrawing from the study for personal reasons. Enrollment was completed in March 2023.

## Discussion

### Comparison to Prior Work

While low levels of physical activity have been a public health concern, there is evidence that sedentary behavior duration may also confer health risks [13]. Observational studies suggest that breaking up sedentary time is associated with improved cardiometabolic health [58]. These free-living, mainly observational studies have demonstrated the theoretical feasibility of workplace interventions, yet cannot control for potentially confounding factors, obscuring the meaningful analysis of the relationship. Laboratory studies, however, suggest a causal relationship between decreased sedentary time and cardiometabolic health [59]. While these studies are tightly controlled in both the environment and intervention, they lack important context regarding the translation of these findings into real-world settings.

The WorkWell Study is a novel randomized controlled crossover trial that has been designed to extend laboratory-based, controlled study designs into the natural environment of the workplace. To accomplish this, we have used digital health technologies to monitor and prompt participants in real time while maintaining rigorous adherence to increased standing and moving regimes. This innovation will allow us to test the effects of breaking up sitting with standing and LPA over a longer period of intervention than has been used in traditional laboratory-based studies. Additionally, we have included a broad set of concomitant biological measures, including dynamic changes in postprandial and 24-hour glucose, as well as outcomes in the emerging areas of metabolome and gut microbiome composition. We will use two 2-week interventions targeting behavior change to decrease sitting time in the workplace as well as to improve cardiometabolic health and to assess behavior change. This study was carefully designed to extend laboratory-based studies—both in duration, as well as translation into more ecological settings—thus providing more evidence on the causal role of interrupted sitting time (with standing and moving) on cardiometabolic health. As a result, we will be able to address (1) statistical association via baseline and washout weeks that allow participants to serve as their own controls, (2) temporality via continuous accelerometer tracking and prescheduled laboratory visits, and (3) nonspuriousness via randomized assignment and controlled treatment dosage.

### Strengths and Limitations

Our project attempts to achieve levels of internal validity previously found only in laboratory-based studies while simultaneously maximizing external validity. While others have demonstrated the benefit of breaking up sedentary behavior in either highly controlled laboratory environments or ecological environments, we will use emerging technologies (ie, wearable sensors and smartphone apps) to deliver a rigorous clinical trial within an employee's real-life workspace. Despite this important strength, some potential challenges warrant discussion. Recruitment and retention of participants in longitudinal research is challenging. We hope to overcome this challenge by allowing participants to engage in the study in their typical work setting, rather than having participants carry out the intervention in a laboratory setting. If successful, this approach will add important information to our current understanding of how best to intervene and engage participants in reducing sedentary time in workplace settings. Participants may also feel uneasy about collecting fecal samples. To ensure this is not a barrier for successful completion of the trial, the study team will provide participants with a discrete collection kit that can be used mostly anywhere that is comfortable for the participant. Delivery of samples to the research facility can then be initiated by the participant or the study staff can retrieve the sample at a place of convenience for the participant. This method has been used by our investigative team in previous studies and has proven beneficial for ensuring receipt of quality samples within the required time frame.

With a wide range of expertise represented on our research team, we are able to consider outcomes in the behavioral, physiological, and microbial realms and are able to examine our outcomes in an integrated and transdisciplinary fashion. While previous research has broadly examined some of these factors, our design and transdisciplinary approach will allow for a more global viewpoint of the influence of breaking up sedentary time during the workday on cardiometabolic health. Currently, the biological and metabolic underpinnings of sedentary behavior-linked disease are grossly understudied. Previous observational work has highlighted potential microbial and metabolic derangements [60-63], but these findings have not been extended to longitudinal interventions, leaving the previous work highly correlational. Our team is well-positioned to advance this area of study toward better mechanistic understandings of sedentary behavior and how intervention in real-world settings can improve health.

### Conclusions

The WorkWell Study is a randomized controlled crossover trial examining the feasibility and impact of breaking up sedentary behavior on cardiometabolic health using the scientific rigor of a laboratory-based study with the context and translatability of a free-living setting. We will explore the effects that standing or moving 6 additional minutes per hour has on postprandial glucose and other physiological measures in the real-world workplace and assess intervention feasibility. Using a rigorous transdisciplinary approach, we seek to fill gaps in previous research and contribute to a more comprehensive picture of the beneficial effects of breaking up sitting behavior.

## Abbreviations

CGM: continuous glucose monitoring
f-FMD: femoral artery flow-mediated dilation
HbA_1c_: hemoglobin A_1c_
HDL: high-density lipoprotein
iAUC: incremental area under the curve
LDL: low-density lipoprotein
LPA: light-intensity physical activity
MS: mass spectrometry
MVPA: moderate to vigorous physical activity
REDCap: Research Electronic Data Capture
TAC: total antioxidant capacity
TEQ: Treatment Evaluation Questionnaire
